## **12. The storage procedure of subject's code, random number table, and case report form**

Each participant will be given a unique screening number, and enrolled participants will be given a unique enrollment number. The trial will be conducted using single-arm sequential enrollment without randomization. Beginning with screening, a dedicated case report is established for each subject. Relevant storage procedures are handled in accordance with the management regulations of clinical research institutions.

### **13. The recording requirement of adverse event (AE) and the reporting, handling, follow-up visit, timing and outcome of serious AE**

#### **13.1 Definition**

##### **13.1.1 Adverse Event (AE)**

AE is any adverse medical event observed after the use of a trial drug in the subject, regardless of whether it is treatment related.

The difference between an AE and an adverse reaction: an adverse reaction means that there is a causal relationship between therapeutic drug and adverse reaction; an adverse event indicates that the causal relationship between therapeutic drug and adverse event is not confirmed, requiring further analysis and evaluation.

##### **13.1.2 Serious Adverse Event (SAE)**

SAEs are any undesirable clinical events occurring at any dose, such as death, life-threatening, hospitalization or prolongation of hospitalization to treat AEs, persistent or significant disability, congenital anomaly or birth defect.

An adverse event should be reported to the sponsor by the research center within 24 hours if the adverse event meets one of the following criteria and is diagnosed as serious adverse event:

Death: the death of subject resulting from adverse event;

Life-threatening: in the opinion of the investigator, an adverse event is likely to result in the immediate death of the subject without medical intervention, excluding the adverse event that occurs more seriously, and already results in death;

Hospitalization: admission to the hospital that is a result of the adverse event, not including emergency or outpatient visit;

Prolongation of hospitalization: adverse event occurs during the subject's hospitalization, which leads to the prolongation of hospitalization for AE therapy;

Persistent or significant loss of function or disability: the subject is unable to perform normal daily activities. Loss of function does not include relatively minor medical events, such as headache, nausea, emesis, diarrhea, influenza and accidental trauma (e.g., sprained ankle);

Important medical event: the event may not result in immediate death, life-threatening or hospitalization, but the important medical event may jeopardize the subject and require medical or surgical intervention to prevent any of the events above (i.e., death, life-threatening, hospitalization

or prolongation of hospitalization, etc.). For example, allergic bronchospasm requiring treatment in the emergency room or at home, convulsions that do not require hospitalization, cachexia, drug dependence or substance abuse, etc.

The hospitalization due to the progression of the original disease is not considered as serious adverse event. The hospitalization resulting from elective surgery and examination or other treatments that are scheduled prior to entering into this trial, or social reasons.

#### 13.1.3 Adverse Drug Reaction (ADR)

For the drug not yet approved for marketing, an adverse reaction is an uncomfortable and unexpected reaction associated with the administration of drug at any dose. There is a causal relationship, or at least a reasonable possibility, between the adverse reaction and the administration of the drug.

#### 13.1.4 Unexpected Adverse Drug Reaction (UADR)

An unexpected adverse drug reaction is an adverse reaction, the nature or severity of which is not consistent with the current product information (e.g., expected adverse events not listed in the investigator's brochure).

The "expected" or "unexpected" adverse reaction is distinguished on the basis of the events observed previously and cannot be predicted from the pharmacological property of drug: ① for drugs not yet approved for marketing, the investigator's brochure is used to determine whether the nature or severity of adverse reaction is consistent with the information described in the investigator's brochure; ② new clinically meaningful information on the nature and severity of a known and documented serious adverse event is also classified as an unexpected adverse reaction.

### 13.2 Severity of adverse event

The severity of adverse event, not associated with ear, should be judged according to the NCI-CTCAE v5.0.

The severity of anticipated adverse events in the ear is defined in terms of mild, moderate, severe, and life-threatening:

Mild/Grade 1: discomfort that not interfere with daily activities; children at 8 kHz with a threshold shift of 20 dB hearing loss; sensorineural hearing loss above 4 kHz in at least one ear.

Moderate/Grade 2: discomfort interfering with daily activities; children at 4 kHz with >20 dB threshold shift in one ear.

Severe/Grade 3: inability to work or perform daily activities; hearing loss requiring therapeutic intervention, including hearing aids; threshold shift of 20 dB in at least one ear at  $\geq 2$  kHz.

Life-threatening /Grade 4: Adverse event may lead to death; cochlear implant; threshold shift of  $>40$  dB of hearing loss, sensorineural hearing loss at  $>2$  kHz.

Death/Grade 5.

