### 3.1 Dose limiting toxicity (DLT)

Dose limiting toxicity (DLT) is evaluated within 42 days after administration of RRG-003 according to Common Terminology Criteria for Adverse Events, NCI-CTCAE V5.0. DLT is defined as hematologic toxicity  $\geq$  grade 4, nonhematologic toxicity  $\geq$  grade 3, or aural toxicity in grade 2 or 3 within 6 weeks. Aural toxicity was listed as follow:

| Adverse Events               | Grade 2 ear adverse events                                                                                  | Grade 3 ear adverse events                                                                              |
|------------------------------|-------------------------------------------------------------------------------------------------------------|---------------------------------------------------------------------------------------------------------|
| Ear pain                     | Moderate pain; limiting instrumental Activities of Daily Living (ADL)                                       | Severe pain; limiting self care ADL                                                                     |
| External ear pain            | Moderate pain; limiting instrumental ADL                                                                    | Severe pain; limiting self care ADL                                                                     |
| Hearing impaired (Pediatric) | Pediatric (on a 1, 2, 3, 4, 6, and 8 kHz audiogram):
Threshold shift >20 dB at 4 kHz in at least one ear | Pediatric (on a 1, 2, 3, 4, 6, and 8 kHz audiogram):
Hearing loss sufficient to indicate therapeutic |

|                                                |                                                                                                                                 |                                                                                                                                                                                                         |
|------------------------------------------------|---------------------------------------------------------------------------------------------------------------------------------|---------------------------------------------------------------------------------------------------------------------------------------------------------------------------------------------------------|

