|                                                |                                                                                                                                 | intervention, including

hearing aids; threshold shift

>20 dB at 2 to < 4 kHz in at

least one ear                                                                                   |
| Middle ear inflammation                        | Serous otitis, medical

intervention indicated                                                                            | Mastoiditis; necrosis of canal

soft tissue or bone                                                                                                                                               |
| Tinnitus                                       | Moderate pain; limiting

instrumental ADL                                                                                 | Severe pain; limiting self care

ADL                                                                                                                                                              |
| Vertigo                                        | Moderate pain; limiting

instrumental ADL                                                                                 | Severe pain; limiting self care

ADL                                                                                                                                                              |
| Vestibular disorder                            | Moderate pain; limiting

instrumental ADL                                                                                 | Severe pain; limiting self care

ADL                                                                                                                                                              |
| Ear and labyrinth disorders-
Other, specify | Moderate; minimal, local or

noninvasive intervention

indicated; limiting age-

appropriate instrumental ADL | Severe or medically significant

but not immediately life-

threatening; hospitalization or

prolongation of existing

hospitalization indicated;

limiting self-care ADL |

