| Otitis externa                                 | Oral intervention indicated

(e.g., antibiotic, antifungal, or

antiviral)                                          | IV antibiotic, antifungal, or

antiviral intervention

indicated; invasive

intervention indicated                                                                                    |
| Otitis media                                   | Localized; oral intervention

indicated (e.g., antibiotic,

antifungal, or antiviral)                               | IV antibiotic, antifungal, or

antiviral intervention

indicated; invasive

intervention indicated                                                                                    |

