## 15.2 Statistical analysis plan

Descriptive statistics are primarily used to analyze trial results. In general, measurement data will list the number of observational cases, mean, standard deviation, median, quartile, maximum and minimum. Enumeration data will list frequency and relative frequency. Unless otherwise specified, all of statistical tests will perform two-tailed test with a 95% confidence interval. Statistical analysis will be performed in a version of SAS 9.4 or higher version.

Use descriptive statistics to describe the number and proportion of subjects entering each analysis set, the number and proportion of subjects completing the trial and withdrawing consent, and the reasons for withdrawing consent (and proportion of subjects) for each dosage group; to describe the baseline characteristic of each dosage group.

Use the Safety Analysis Set to summarize treatment-emergent adverse event (TEAE) and adverse reaction for each dosage group; the AEs, occurs after signing informed consent and before treatment, will be only tabulated based on per subject and not summarized. TEAE is defined as the adverse event that is not present before dosing and occurs within 28 days (inclusive) after administration. The severity of adverse event and adverse reaction will be graded based on the NCI-CTCAE v5.0. Adverse event and adverse reaction will further be summarized based on System Organ Class and Preferred Term.

Using the safety analysis set baseline data, post-dosage data, and change from baseline were summarized for each follow-up visit and each dosage group, according to safety data such as laboratory, vital signs, electrocardiogram, physical examination, and otologic examination. Shift tables will be used to describe change from baseline after each follow-up visit to determine whether each examination result was normal and clinically significant as categorical data.

Use Per-Protocol Set to summarize efficacy data at each efficacy evaluation point and plot the efficacy-time curve of each subject, the mean efficacy-time curve of each dosage group, and the mean efficacy-curve of all subjects, according to efficacy data change from baseline in each dosage group.

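### Ear adverse events have no single grading scale in protocol v5: sections 3.1, 13.2 and 15.2 disagree, and the hearing grades in 13.2 overlap

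*Supplement*

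**What the plan says.** Three sections of protocol v5 bear on the grade of an ear event.

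- **Section 3.1 (DLT).** Toxicity is assessed "according to Common Terminology Criteria for Adverse Events, NCI-CTCAE V5.0", and the DLT definition includes "aural toxicity in grade 2 or 3 within 6 weeks". A printed ear table follows, with columns for grades 2 and 3 only. In its hearing row, grade 2 is "Threshold shift >20 dB at 4 kHz in at least one ear". Grade 3 is a shift ">20 dB at 2 to < 4 kHz in at" least one ear, or hearing loss that calls for treatment such as a hearing aid. Otitis externa is grade 2 when there is "Oral intervention indicated", and localized otitis media is graded the same way.
- **Section 13.2 (severity).** "The severity of adverse event, not associated with ear, should be judged according to the NCI-CTCAE v5.0". Anticipated ear events get a separate scale. Its hearing criteria are: grade 1, 20 dB at 8 kHz or sensorineural loss above 4 kHz; grade 2, more than 20 dB at 4 kHz; grade 3, a "threshold shift of 20 dB in at least one ear at" 2 kHz or above; grade 4, more than 40 dB, above 2 kHz. The other main criterion is interference with daily activities. Infection is not mentioned.
- **Section 15.2 (analysis plan).** "The severity of adverse event and adverse reaction will be graded based on the NCI-CTCAE v5.0". No exception is made for the ear.

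No section says which of these prevails.

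**The concern.** Sections 13.2 and 15.2 cannot both be followed for an ear event: one takes it out of CTCAE and the other puts it back. Section 13.2 cannot be followed alone either, because one hearing shift can meet two or three of its grades and no rule picks between them. Two careful coders could fill the same severity table differently.

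This matters more here than in a larger trial. Section 11 makes DLT at week 6 the primary indicator, and section 3 acts on single events at 50 µL: 3 to 5 participants without a DLT allow extension, whereas one DLT in the second or third participant requires three more. Section 5 plans 4-12 effective cases in all. Section 13.8.2 also handles events differently during DLT observation according to whether they meet the DLT definition. A reader must be able to trace an ear event from its recorded grade to its DLT status, and the text does not allow that.

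**Working it through.** The plan states no figure to reproduce, so the check sets the hearing criteria of 3.1 and 13.2 side by side.

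**Inputs.** The frequencies are those of the 3.1 audiogram: 1, 2, 3, 4, 6 and 8 kHz. Single-frequency shifts of 15, 20, 25 and 45 dB were chosen to straddle the 20 and 40 dB cut-offs, giving 4 × 6 = 24 cells.

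**Reading assumed.** A shift of 20 dB in 13.2 means 20 dB or more, and such a shift above 4 kHz counts as sensorineural loss there. For 3.1 only the dB and kHz criteria are coded; its treatment-based criterion and its residual row for other ear disorders are left out.

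| Shift and frequency | 3.1, dB/kHz part | 13.2 |
|---|---|---|
| 20 dB at 2, 3 or 4 kHz | neither grade 2 nor 3 | 3 |
| 20 dB at 6 or 8 kHz | neither | 1 and 3 |
| 25 dB at 2 or 3 kHz | 3 | 3 |
| 25 dB at 4 kHz | 2 | 2 and 3 |
| 25 dB at 6 or 8 kHz | neither | 1 and 3 |
| 45 dB at 2 kHz | 3 | 3 |
| 45 dB at 3 kHz | 3 | 3 and 4 |
| 45 dB at 4 kHz | 2 | 2, 3 and 4 |
| 45 dB at 6 or 8 kHz | neither | 1, 3 and 4 |

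A 15 dB shift, or any shift at 1 kHz alone, meets no dB/kHz criterion in either section.

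**Overlap within 13.2.** It grades 5 frequencies × 3 shifts = 15 cells. More than one grade applies in 2 (20 dB) + 3 (25 dB) + 4 (45 dB) = 9 of them. Taking the highest grade met would remove the ambiguity, but the plan does not say so. It would also leave the 4 kHz criterion of grade 2 and the 8 kHz criterion of grade 1 unusable, since every shift meeting either also meets grade 3.

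**What if 13.2 grades were put into the 3.1 DLT rule?** The documents do not direct this; it shows what the missing precedence statement leaves open. Grade 4 is counted as a DLT through the clause on nonhematologic toxicity of grade 3 or more.

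- Highest 13.2 grade: DLT status differs from 3.1 in 5 (20 dB) + 2 (25 dB) + 2 (45 dB) = 9 of 24 cells.
- Lowest 13.2 grade: it differs in 3 of 24 (exactly 20 dB at 2, 3 and 4 kHz).
- If 13.2 is instead read as more than 20 dB, the five 20 dB differences vanish. The counts become 9 − 5 = 4 with the highest grade and 3 − 3 = 0 with the lowest.

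The differences at 6 and 8 kHz hold only where no other 3.1 criterion is met. These cells are not equally likely events; the counts describe the text, not the expected number of children.

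**Infection.** Section 13.8.1 lists otitis media among expected reactions, so the 13.2 scale for anticipated ear events appears to cover it. If oral treatment is indicated, 3.1 gives grade 2 and hence a DLT. Section 13.2 offers only discomfort and interference with activities, which could yield grade 1 if activities are unaffected.

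**The case against.** The strongest reply is that only 3.1 defines a DLT. It prints its own ear table directly under the definition, and 13.2 never mentions DLT. Read this way, the primary endpoint has one rule and the conflict is confined to severity reporting. It can be added that 3.1 and 15.2 name the same scale, so 13.2 is the outlier. Both points stand. They narrow the problem without removing it: 13.2 still contradicts 15.2, still overlaps with itself, and no sentence gives 3.1 precedence.

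Four stronger inferences are tempting but unsupported.

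- *The same event is a DLT under one section and not under another.* Section 13.2 makes nothing a DLT; the discordant counts arise only by carrying its grades into the 3.1 rule.
- *Shifts at 6 and 8 kHz can never be a DLT under 3.1.* Grade 3 in the hearing row also covers hearing loss calling for treatment, with no frequency limit, and the residual row is a further route.
- *A cochlear implant placed because the vector did not work would be counted as grade 4 toxicity.* Section 13.2 grades anticipated adverse events, and nothing makes lack of effect an adverse event. Section 4.3 treats a need for other treatment within the 6-week period as withdrawal.
- *Events already recorded have been misgraded.* The documents show no recorded ear events.

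The practical frequency is also unknown. Children enter with hearing loss of at least 65 dB, and pure-tone testing is done only if the child cooperates, so isolated single-frequency worsening may be rare or hard to measure.

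**Conclusion.** The plan is wrong as written on severity grading of ear events. Sections 13.2 and 15.2 contradict each other, the 13.2 hearing cut-offs differ from those in 3.1, and 13.2 gives more than one grade in 9 of the 15 grid cells it grades. Severity tables cannot be reproduced from the text and need not agree with the DLT count.

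For the primary endpoint the conclusion is weaker. Section 3.1 most naturally governs the DLT, in which case DLT status does not depend on 13.2. Because this is nowhere stated, the exposure is conditional. If 13.2 grades were used, status could change for a shift of exactly 20 dB at 2-4 kHz, for isolated 6 or 8 kHz shifts that meet no other 3.1 criterion, and possibly for otitis needing oral treatment without interference with activities. That is 0 to 9 of the 24 hearing cells, depending on how 20 dB is read and which overlapping grade is taken. Whether the 3.1 table reproduces CTCAE v5.0 cannot be checked from the documents, and the conclusion does not need it.

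**What to change.** Reconcile the three sections around one ear table.

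1. In 3.1, keep one ear table and extend it to every grade that will be reported. Map each combination of shift size and frequency to exactly one grade, and say how infections are graded. The sponsor and investigators choose the cut-offs; this review takes no view on which are right.
2. State in 3.1 that this table governs both DLT assessment and severity reporting of ear events.
3. Replace the ear wording in 13.2 with a reference to the table.
4. State in 15.2 that ear events are graded by the table and all other events by CTCAE v5.0.
5. Apply the same table to all ear events in the analysis, whenever they occurred, and fix the cut-offs without reference to which events would change grade.

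The cost is wording in three sections and an ethics submission for the amendment. It adds no participants, visits or tests. If the existing 3.1 criteria for grades 2 and 3 are kept and 3.1 already governs, the DLT count is unchanged; if they are altered, the DLT definition itself changes and the amendment should say so.

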### 13.3 Judgement of the causal relationship between adverse event and the investigational drug

At present, the causal relationship between adverse event and medication administration is usually classified into 5 cases in China and internationally:

- a) Definite Related: adverse event occurs explained by drug administration;
- b) Probably Related: adverse event occurrence probably highly related to drug administration;
- c) Possibly Related: adverse event occurrence possibly related to drug administration;
- d) Unlikely to be Related: adverse event occurs more likely to be related to another factor;
- e) Not Related: adverse event due to other significant factors.

Items ① to ③ above should be recorded as adverse drug reactions. Incidence of adverse reaction = number of (① + ② + ③) cases/number of cases in safety data set  $\times 100\%$ .

The causal relationship between adverse event and medication administration

|                                                                                                                              | ①
Definite
Related | ②
Probably
Related | ③
Possibly
Related | ④
Unlikely
to be
Related | ⑤Not
Related |
|------------------------------------------------------------------------------------------------------------------------------|--------------------------|--------------------------|--------------------------|-----------------------------------|-----------------|
| Temporal relationship: a reasonable temporal relationship between drug administration and the occurrence of reaction / event | +                        | +                        | +                        | +                                 | -               |
| Known: the reaction that is consistent with known adverse reaction of drug                                                   | +                        | +                        | +                        | -                                 | -               |
| Dose-response relationship:                                                                                                  | +                        | +                        | $\pm$                    | $\pm$                             | -               |

|                                                                                                                                                                         |   |   |   |   |   |
|-------------------------------------------------------------------------------------------------------------------------------------------------------------------------|---|---|---|---|---|
| disappearance or reduction of reaction/event after drug withdrawal or dose reduction                                                                                    |   |   |   |   |   |
| Recurrence: reaction/event that reoccurs after a rechallenge                                                                                                            | + | ? | ? | ? | - |
| Explainable: reaction/event that is not explained by the effect of the concomitant medications, the progression of subject's condition, the effect of other treatments. | + | + | - | ± | - |

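### The causality grid in section 13.3 grades a plausibly timed reaction that is new in nature and has no other explanation as Unlikely, so it drops out of the adverse-reaction incidence

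*Supplement*

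**What the plan says.** All references are to the Supplement, Trial Protocol version 5.0.

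- **13.3, category wording.** Five categories run from Definite to Not Related. Unlikely is described as the case where another factor is the more probable cause.
- **13.3, counting rule.** The first three categories "should be recorded as adverse drug reactions". The incidence is the number of cases in those three categories divided by the number in the safety data set.
- **13.3, grid.** Each category is scored on five rows:
  - time course: "Temporal relationship: a reasonable temporal relationship between drug administration and the occurrence of reaction / event"
  - precedent: "Known: the reaction that is consistent with known adverse reaction of drug"
  - withdrawal or dose reduction: "disappearance or reduction of reaction/event after drug withdrawal or dose reduction"
  - rechallenge: "Recurrence: reaction/event that reoccurs after a rechallenge"
  - other causes: "Explainable: reaction/event that is not explained by the effect of the concomitant medications, the progression of subject's condition, the effect of other treatments"
- **13.1.3.** A reasonable possibility of a causal link is enough for an adverse drug reaction. No prior knowledge of the reaction is required.
- **13.1.4.** "An unexpected adverse drug reaction is an adverse reaction, the nature or severity of which is not consistent with the current product information". An unexpected reaction is thus still an adverse reaction.
- **15.2.** Adverse reactions are summarised by dosage group on the Safety Analysis Set, and further by System Organ Class and Preferred Term.

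**The concern.** Whether a reaction has been seen before bears on whether it is expected. It should not decide whether the drug caused it. The grid makes precedent a condition for every category that counts as drug-related. An investigator who follows it must grade a well-timed, otherwise unexplained new event as Unlikely, although the text keeps that category for events better explained by something else.

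The primary purpose is safety and tolerability (section 2.1), and the protocol cites no human data for RRG-003. Reactions without precedent are therefore a realistic possibility. At stake are the reported adverse-reaction incidence, its breakdown by dose, and the recognition of reactions that are unexpected in nature.

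**Working it through.** The plan states no figure to reproduce. The check is a trace of the grid followed by simple arithmetic on the incidence formula.

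**Inputs (version 5.0, section 13.3).**

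| Row | Definite | Probable | Possible | Unlikely | Not Related |
|---|---|---|---|---|---|
| Temporal | + | + | + | + | − |
| Known | + | + | + | − | − |
| Withdrawal / dose reduction | + | + | ± | ± | − |
| Rechallenge | + | ? | ? | ? | − |
| Not otherwise explained | + | + | − | ± | − |

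**Step 1: plausible timing, no precedent.** With temporal + and known −, the other rows allow 2 (withdrawal) × 3 (rechallenge +, −, unknown) × 2 (explained or not) = 12 profiles.

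- If the question mark accepts any result, all 12 match Unlikely and no other column.
- If it means strictly that rechallenge is unknown, the 4 profiles with unknown rechallenge match Unlikely only, and the other 8 match no column.
- Under either reading, none of the 12 reaches Definite, Probable or Possible.

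The profile of interest is temporal +, known −, rechallenge unknown, not otherwise explained +. It is graded Unlikely whatever the withdrawal result.

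**Step 2: the Explainable row.** A plus here means that no other cause accounts for the event. Possible requires a minus, while Unlikely accepts either, so the weaker category tolerates the stronger evidence. This leaves a gap. Take an event that is known and well timed, has no other explanation and does not resolve (withdrawal −):

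- Definite and Probable fail on the withdrawal row.
- Possible fails on the Explainable row.
- Unlikely fails on the Known row.
- Not Related fails on the temporal row.

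It fits no column under either reading of the question mark.

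**Step 3: comparison with the text.**

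- The grid sends an event with no other explanation to a category worded for events that another factor explains better.
- Section 13.1.3 would count the same event, because a reasonable possibility is enough.
- Section 13.1.4 treats a reaction whose nature is not in the product information as an adverse reaction. The grid cannot place such a reaction among the three counted categories.

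**Step 4: size.** Incidence = counted cases / safety set × 100%. One child moved from counted to not counted changes it by 1/n:

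- n = 12: 1/12 = 8.3 percentage points
- n = 6: 1/6 = 16.7 percentage points
- n = 4: 1/4 = 25.0 percentage points

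These n are assumed from the 4-12 effective cases in section 5; the safety-set size is not given. The arithmetic also assumes that each child counts once and has no other counted reaction. If there is another, the overall figure does not move, but the figure for the specific reaction does.

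**The case against.** The strongest defence is that the grid is only an aid. The verbal categories come first, the counting rule can be read as pointing to them, and section 13.5 asks for a relatedness judgement where one can be made. The grid also leaves some profiles without a column, so judgement must fill gaps anyway. An investigator could follow 13.1.3 and grade a new event as Possible. This stands in part: a zero count is not certain in practice. But no text calls the grid advisory or exempts new reactions. Discretion would let two investigators grade the same event differently, which does not mend the rule.

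Four stronger readings are tempting, and the documents do not support them.

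- **That toxicity is hidden.** All adverse events are recorded regardless of relatedness (13.5). TEAEs are tabulated by dose group (15.2). The DLT definition has no attribution condition (3.1), and DLTs, not adverse reactions, drive escalation. SAEs are reported within 24 hours whatever their cause (13.6).
- **That any new ear or systemic event is lost.** Section 13.8.1 already lists many reactions to AAV drugs, inner-ear injection and steroids, including vestibular dysfunction, hearing loss, tinnitus and hepatotoxicity. If that list defines what is known, which the grid does not say, those events score + and the affected set is narrower.
- **That the unexpected-reaction class must stay empty.** Section 13.1.4 also covers unexpected severity and new information on a known serious event. Such reactions can score + on Known. Only those unexpected in nature are affected.
- **That rechallenge can never be scored.** Version 5.0 allows one or two injections, including repeat dosing of one ear (sections 3 and 6.1). The difficulty arises for children with no second exposure.

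The documents also do not describe the trial as first-in-human. That would be inferred from the absence of cited human data.

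**Conclusion.** The point holds. As written, the grid excludes a plausibly timed, otherwise unexplained reaction that is new in nature from the three counted categories, against 13.1.3, 13.1.4 and the category wording. It also has no place for a known, otherwise unexplained event that does not resolve.

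The bias in the incidence is downward, by about 8 to 25 percentage points per affected child under the assumed safety-set sizes. How many children would be affected cannot be said from the documents: it depends on what counts as known, which is undefined, and on how strictly investigators apply the grid.

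The effect is confined to the adverse-reaction classification, its incidence and its summary by dose. The primary indicator is not touched. Severity is moderate.

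**What to change.** Reconcile the grid with 13.1.3, 13.1.4 and the category wording:

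1. Remove Known as a condition for Definite, Probable and Possible. Use it only to separate expected from unexpected reactions, and name the reference list that defines known.
2. Correct the Explainable row so that a plausibly timed event with no other explanation is at least Possible. One way is ± for Possible and − for Unlikely. Where an event with another possible cause then fits both, the category wording decides, by whether that other cause is the more probable one.
3. Allow the withdrawal/dose-reduction and rechallenge rows to be scored not applicable where there was no such opportunity, for example after one injection, without lowering the category. State whether Definite stays open without a rechallenge; this choice does not affect the incidence, because the first three categories count alike.
4. Keep the incidence formula.

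The cost is one edited table, plus a re-check of any attribution already made with the present grid. The reported adverse-reaction incidence may rise somewhat.
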